## Abstract

**Background:**

Young adults’ drinking habits commonly exceed recommendations for low-risk drinking, which may have a negative effect on their mental, social, and physical health. As smartphones are highly accessible to young adults, mobile apps could be used to support young adults to develop low-risk drinking habits and improve their general health.

**Objective:**

The objective of this study is to evaluate the effectiveness of Boozebuster, a self-guided mobile app based on healthy lifestyle–related components that aim to develop and maintain low-risk drinking habits among young adults.

**Methods:**

This two-arm, parallel-group randomized controlled trial will investigate whether a 6-week self-guided mobile intervention (Boozebuster) targeting drinking behavior is more effective than a minimal intervention consisting of an educational website on alcohol use and its consequences for young adults. We will recruit 506 young adults (aged 18-30 years) from the Netherlands via an open recruitment strategy by using an open access website. All outcomes will be self-assessed through questionnaires. The primary outcome is the quantity and frequency of alcohol consumption in standard drinks (10 g ethanol per standard drink) per month (timeline follow-back [TLFB]). Secondary outcomes include binge-drinking sessions per month, alcohol-related problem severity (Rutgers Alcohol Problem Index), cannabis use frequency and quantity in grams (TLFB), depressive symptoms (Center for Epidemiological Studies Depression Scale), perceived stress (Perceived Stress Scale), engagement (Twente Engagement with eHealth Technologies Scale), readiness to change (Readiness to Change Questionnaire), mental well-being (Warwick-Edinburgh Mental Wellbeing Scale), trauma and COVID-19–related trauma (Short-Form Posttraumatic Stress Disorder Checklist for Diagnostic and Statistical Manual of Mental Disorders, 5th Edition), impulsivity (Urgency, Premeditation, Perseverance, Sensation Seeking, Positive Urgency Impulsive Behavior Scale), study or work performance (Individual Work Performance Questionnaire), and treatment adherence. Baseline (T0), 6-week postbaseline (T1), and 3-month postbaseline (T2) assessments will be conducted and analyzed on the basis of the intention-to-treat principle using multilevel mixed modeling analyses.

**Results:**

Recruitment began in September 2020. We received 933 registrations via our study information website; 506 participants have completed the T0 assessment, 336 participants have completed the T1 assessment, and 308 participants have completed the T2 assessment as of May 2021. The study is still in progress, and results will be reported in 2021 and 2022.

**Conclusions:**

Self-guided mobile interventions based on a lifestyle approach might be an attractive approach for young adults due to their preference on self-reliance, healthy living, and increased perceived anonymity. Such interventions are yet understudied, and it is known that interventions addressing solely problem drinking are less appealing to young adults. We hypothesize that the Boozebuster mobile app will effectively reduce drinking levels compared to an alcohol educational website (control condition). If effective, our intervention could be an inexpensive and scalable public health intervention to improve drinking habits in young adults.

**Trial Registration:**

Netherlands Trial Register NL8828; https://www.trialregister.nl/trial/8828

**International Registered Report Identifier (IRRID):**

DERR1-10.2196/29750

## Introduction

It is well known that the prevalence of alcohol consumption among young adults is high and that their drinking habits commonly exceed low-risk drinking guidelines [1]. A study by the Dutch National Institute for Public Health and the Environment (Rijksinstituut voor Volksgezondheid en Milieu) showed, for example, that 8.9% of young adults were considered problem drinkers, defined as individuals who drink more than 21 standard glasses of alcohol per week for males and more then 14 standard glasses of alcohol per week for females. Alcohol consumption among young adults is characterized by a drinking pattern that differs from the general population. Specifically, we know that young adults are more likely to binge drink, especially during the weekends [2]. In addition, binge drinking occurs in about 11.4%-19.4% of young adults (18-29 years of age) compared to approximately 7.7% of the general population [3]. Consequently, young adults’ drinking patterns pose a significant negative effect on young adults’ mental, social, and physical health [4].

According to the literature, face-to-face interventions delivered in individual or group settings targeting young adults’ drinking patterns are effective [5,6]. However, given that young adults commonly avoid traditional counseling services due to perceived stigma and their preference for self-reliance [7,8], a potential solution to overcome these obstacles might be to provide self-guided digital interventions, which require limited resources compared to traditional prevention and treatment services.

Ample digital interventions that are aimed to reduce drinking levels in young adults, mostly in university settings located in the United States or Australia, have been previously evaluated. The majority of these interventions consist of internet-based single-session interventions, based on personalized normative feedback (PNF), that aim to correct erroneous perceptions of peer drinking levels by assessing personal drinking levels and consequently comparing them with drinking levels in similar-aged peer groups [9]; general alcohol education programs that are commonly incorporated within general education curriculums and provide educational modules about alcohol use, its dangers, and often focus on ensuring students comply with the law [10]; or brief interventions that screen for problematic drinking patterns and present feedback motivating individuals to alter those patterns [11].

The majority of the above-described digital interventions are delivered via a computer or web browser. However, it has been claimed that mobile apps are more suitable for young adults given the flexibility, interactivity, and their spontaneous nature [12]. However, a recent review assessed mobile apps developed with the purpose of managing alcohol consumption found that the evidence is promising but still inconclusive given the mixed results [13].

Although single-session interventions can reach a high number of individuals due to their appealing, limited time requirement, they are associated with a few important disadvantages such as the relatively small effect sizes produced and the limited longevity of those effects. For example, meta-analyses assessing single-session interventions show small effect sizes when compared to assessment only, attention-matched, or active controls ranging from g=0.18 to g=0.29 [5,14-18]. In addition, studies that assess long-term outcomes often show that those effects cease to exist in follow-up periods [19]. Lifestyle medicine is a relatively new approach for the potential prevention, promotion, and management of mental health conditions. It involves the use of environmental, behavioral, and psychological principles to improve physical and mental well-being by modifying lifestyle factors such as diet, physical activity, relaxation, sleep, and stress [20]. Although lifestyle modification has been extensively studied in particular regarding the prevention of chronic diseases [21], research about its value in curbing drinking among young adults is very limited. However, studies have shown that digital lifestyle interventions that target multiple behaviors may increase and prolong the effectiveness of behavioral change interventions targeting young adults [22-24].

Therefore, in our intervention, we decided to incorporate relevant lifestyle components that have been shown to be perceived as relevant and important for our target group’s general well-being [25-27]. Such lifestyle-related topics include sleeping habits, mood, and perceived stress. We expect that by providing young adults with relevant lifestyle components in addition to the alcohol-related intervention content, we have a potential to increase and prolong effect sizes regarding drinking outcomes, while retaining the acceptability and reach of single-session interventions.

## Methods

### Study Design

We will conduct a two-arm, parallel-group randomized controlled trial (RCT) comparing a 6-week mobile app (Boozebuster) with an active educational website control condition. Participants in the Boozebuster condition will receive access to the self-guided mobile app; participants in the control condition will receive access to an educational website containing information about the effects and consequences of alcohol use on health. The Scientific and Ethical Review Committee of the Faculty of Behavioral and Movement Sciences of the Vrije Universiteit Amsterdam has approved the study protocol, informational letter, and informed consent process. The primary and secondary outcomes in addition to the exact timepoints at which each measure will be applied is presented in Table 1. The study is registered with the Netherlands Trial Registry (NL8828).

**Table 1 table1:** Overview of study measurements, timepoints, and instruments.

Outcome measures	Baseline (T0)	6-week postbaseline (T1)	3-month postbaseline (T2)
Sociodemographics	✓		
Alcohol consumption, frequency, and quantity (TLFB^a^)	✓	✓	✓
Binge-drinking frequency	✓	✓	✓
Cannabis consumption, frequency, and quantity (TLFB)	✓	✓	✓
Depressive symptoms (CES-D^b^ Scale)	✓	✓	✓
Perceived stress (PSS^c^)	✓	✓	✓
Alcohol-related problem severity (RAPI^d^)	✓	✓	✓
Readiness to change (RCQ^e^)	✓	✓	
Task performance (IWPQ^f^)	✓	✓	✓
Engagement (TWEETS^g^)	✓	✓	
Mental well-being (WEMWBS^h^)	✓	✓	✓
Short-form PCL-5^i^	✓	✓	✓
Short-form PCL-5 – COVID-19	✓	✓	✓
UPPS-P^j^ Impulsive Behavior Scale	✓	✓	✓

^a^TLFB: timeline follow-back.

^b^CES-D: Center for Epidemiological Studies Depression.

^c^PSS: Perceived Stress Scale.

^d^RAPI: Rutgers Alcohol Problem Index.

^e^RCQ: Readiness to Change Questionnaire.

^f^IWPQ: Individual Work Performance Questionnaire.

^g^TWEETS: Twente Engagement with eHealth Technologies Scale.

^h^WEMWBS: Warwick-Edinburgh Mental Wellbeing Scale.

^i^PCL-5: Posttraumatic Stress Disorder Checklist for Diagnostic and Statistical Manual of Mental Disorders, 5th edition.

^j^UPPS-P: Urgency, Premeditation, Perseverance, Sensation Seeking, Positive Urgency.

### Inclusion Criteria

Young adults will be eligible for the RCT if they meet the following criteria: (1) aged between 18 and 30 years, (2) willingness to develop healthy lifestyle behaviors and low-risk drinking habits, (3) provision of informed consent digitally, (4) proficiency in reading and writing in Dutch, (5) access to an Android or IOS device with connection to the internet, and (6) possession of an email address. We did not apply a minimum drinking severity inclusion criterion. Our reasoning for not screening drinking severity is based on the fact that the Dutch drinking guidelines recommend an alcohol consumption level of zero or no more than 1 alcoholic drink per day.

### Recruitment

We will make use of an open recruitment strategy, specifically, by means of advertisements on social media and health-related websites and via posters on educational facilities. These advertisements contain a link to our study information website [28]. Interested respondents can apply by leaving their email address, and they will be consequently contacted via email by the research team. The participants will be invited to complete a baseline assessment (T0), 6-week postbaseline assessment (T1), and 3-month postbaseline assessment (T2) via the computerized Castor Electronic Data Capture (EDC) system [29]. All participants will be offered an incentive of €10 (US $12.2) for completing the T1 assessment and an additional €10 (US $12.2) incentive for completing the T2 assessment.

### Randomization

First, participants will be screened, asked to fill out the baseline assessment (T0), and then randomized into either the mobile intervention or the educational website group. The allocation sequence will be automatically generated via the computerized Castor EDC system by using a 1:1 allocation ratio with random block sizes of 4 and 6, which also ensures allocation sequence concealment. Participants will be informed about the outcome of the randomization via email by a member of our research team. Initial stratification will be into two groups according to gender (ie, male and female). Within these two groups, participants will be further stratified into two groups categorized by adherence or nonadherence to the Dutch drinking guidelines. Nonadherence will be defined as the consumption of more than 7 drinks per week or at least one binge-drinking session (≥5 drinks for male participants and ≥4 drinks for female participants) in the past 30 days. This will create four strata. Because of the nature of our study design, blinding of group allocation for participants is not possible. Figure 1 provides an overview of the trial flow.

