### Statistical Analyses

After the data collection period, we will clean our data and assess it for accuracy and completeness. Missing data will be handled using either multiple regression imputation techniques or full information maximum likelihood estimation, depending on the amount of missing data and whether it is missing at random or not. All analyses for the primary and secondary outcomes will use linear mixed modeling regression analyses with the three time points nested within participants. For continuous outcomes, linear models will be used for normally distributed data and negative binomial models, for left-skewed data. For dichotomous outcomes, such as whether or not participants had a binge-drinking episode in the past 30 days, binary logistic regression will be used. All primary analyses will be conducted in line with the intention-to-treat (ITT) principle (ie, including all participants that are randomized). Sensitivity analyses will be conducted in line with the per-protocol principle (ie, intervention completers) and with study completers only. All statistical tests use a significance level α=.05. Time will be used as predictor and baseline measures will be included as covariates if appropriate. All analyses will be conducted using the R Statistical Package. Cohen *d* values will be used as the measure of effect size. Effect sizes of 0.8 are assumed to be large, effect sizes of 0.5 are assumed to be moderate, and effect sizes of 0.2 are assumed to be small [69]. In addition, several intervention effect moderators that might moderate drinking levels based on findings of previous studies will be investigated. In addition, potential moderators such as gender [70], readiness to change [71], engagement [72], and impulsivity [73] will be explored.

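### Randomisation is stratified by gender and guideline adherence, but the analysis commits to neither factor, nor to baseline drinking, as a covariate

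*Protocol article*

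**What the plan says.** All references are to the Methods of the protocol article.

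- **Randomization.** Participants are split by gender, and then "participants will be further stratified into two groups categorized by adherence or nonadherence to the Dutch drinking guidelines". The second factor is a cut of recent drinking: "Nonadherence will be defined as the consumption of more than 7 drinks per week or at least one binge-drinking session" in the past 30 days. The section adds "This will create four strata" and describes a "1:1 allocation ratio with random block sizes of 4 and 6".
- **Statistical Analyses.** The models are mixed regressions on T0, T1 and T2 within participants. The covariate rule is one sentence: "Time will be used as predictor and baseline measures will be included as covariates if appropriate". Gender returns only in the exploratory list: "potential moderators such as gender [70], readiness to change [71], engagement [72], and impulsivity [73] will be explored". Guideline adherence does not appear in this section.
- **Inclusion Criteria.** "We did not apply a minimum drinking severity inclusion criterion".
- **Sample Size.** 253 per arm for g = 0.25, α = .05 and power .80, with no mention of covariate adjustment.

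**The concern.** Stratified blocking balances the arms on gender and on a coarse measure of baseline drinking, so the true sampling variance of the arm difference falls. A model that holds neither the strata nor a close substitute leaves the between-stratum variance in its residual and reports a standard error that is too large. Intervals are then too wide, the test rejects less often than 5% under the null, and precision that the design paid for is lost. The article does give a covariate rule, but a condition with no criterion lets the choice be made after the data are seen.

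The second part concerns the moderators. Non-drinkers and light drinkers may enrol, and their scope to reduce monthly drinks is limited or nil. Whether the app works in people above the guideline is a question the stratification makes answerable, yet only the other design factor, gender, is named as a moderator.

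**Working it through.** **1. The plan's own figure.** Two-sided α = .05, power .80, standardised difference 0.25: n = 2(1.96 + 0.8416)² / 0.25² = 251.2, so 252 per arm. The t-test version gives 252.1, rounded up to the stated 253. Power at 253 is 0.803. A one-sided test would need only 198, so the plan is two-sided. It is a plain two-group calculation that takes no credit for covariates.

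**2. Neither strata nor baseline in the model.** Let R² be the share of outcome variance explained by the strata. The documents do not give it, so a range is assumed. With SE = √(2/253) = 0.0889:

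- reported SE / true SE = 1/√(1−R²)
- type I error = 2[1 − Φ(1.96/√(1−R²))]
- power unadjusted = 1 − Φ((1.96·SE − 0.25)/(SE√(1−R²)))
- power with strata = Φ(0.25/(SE√(1−R²)) − 1.96)

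| R² (assumed) | SE too large by | Type I error | Power unadjusted | Power with strata |
|---|---|---|---|---|
| 0.02 | 1.0% | 0.048 | 0.805 | 0.811 |
| 0.10 | 5.4% | 0.039 | 0.815 | 0.842 |
| 0.20 | 11.8% | 0.028 | 0.830 | 0.882 |
| 0.30 | 19.5% | 0.019 | 0.846 | 0.919 |

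**3. Baseline drinking as a covariate.** This was simulated with 506 participants, four strata, permuted blocks of 4 and 6, one follow-up and 4000 runs per setting. Assumed values: correlation ρ of baseline with follow-up drinking of 0.5 or 0.7, 20% or 40% of participants adherent, and gender acting only through baseline drinking.

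| ρ, adherent share | Type I: none / strata / baseline / both | Power at d = 0.25: none / strata / baseline / both |
|---|---|---|
| 0.5, 20% | .036 / .049 / .050 / .050 | .816 / .843 / .896 / .897 |
| 0.5, 40% | .032 / .046 / .051 / .051 | .830 / .870 / .904 / .904 |
| 0.7, 20% | .025 / .047 / .054 / .055 | .839 / .905 / .979 / .980 |
| 0.7, 40% | .018 / .051 / .055 / .055 | .842 / .915 / .974 / .974 |

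Once baseline drinking is a covariate, adding the strata moves power by 0.1 point or less and the mean SE by about 0.0001.

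**4. T0 only as a repeated response.** The arm comparison is then close to one of change scores. Let s be the strata's share of baseline variance. With unit variances, change has variance 2(1−ρ), and the strata explain (1−ρ)²s of it, a share of (1−ρ)s/2. The simulated SEs at ρ = 0.5 imply s: 1 − (0.0835/0.0889)² = 0.118 = 0.25s, so s = 0.47 (20% adherent); 1 − (0.0821/0.0889)² = 0.147, so s = 0.59 (40% adherent).

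- ρ = 0.5: share 0.118 to 0.147, SE too large by 6.5 to 8.3%. This equals the no-baseline case, because (1−0.5)/2 = 0.5².
- ρ = 0.7: share 0.15 × 0.47 = 0.071 to 0.15 × 0.59 = 0.089, SE too large by about 4 to 5%. Without any use of T0 the share is 0.49s = 0.23 to 0.29, an excess of about 14 to 19%.

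A separate simulation of change scores gave about 4 to 6%, within this range.

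**5. Follow-up numbers so far.** The Results section reports 336 completers at T1 and 308 at T2 as of May 2021. For completers only, with equal arms and no baseline covariate, power without and with strata at R² = 0.10, 0.20, 0.30 is 0.64 v 0.68, 0.64 v 0.73, 0.65 v 0.78 (n = 336), and 0.60 v 0.64, 0.60 v 0.69, 0.61 v 0.75 (n = 308). Most of the gap to 80% is attrition: with R² = 0, power is already 0.63 and 0.59.

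**6. Room to reduce.** The adherent stratum allows at most 7 drinks a week, that is 7 × 30/7 = 30 per 30 days on the primary scale, with no binge session. The lower end is zero.

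**The case against.** The strongest reply is that nothing has been excluded. Gender is known at baseline and adherence is derived from baseline drinking, so the open clause can admit both. The article condenses its model: the sentence that names time does not name treatment arm either, and nobody concludes that arm is left out. A full covariate list may sit in an analysis plan that is not shown. Adherence is also largely a cut of baseline drinking, so adjusting for the baseline timeline follow-back value recovers nearly all of the benefit. This stands in part. It rules out saying that the model omits the strata. It does not turn a conditional clause into a commitment, and the recovery occurs only if baseline drinking is in fact a covariate.

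A reader might also infer that the trial falls below its planned power. The documents do not support that: 80% was planned without covariates, and in the worst case of step 2 power at full N is 0.805 to 0.846.

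Nor is adherence the only moderator built into the design. Gender is the other stratification factor and is listed. The moderator list is open-ended and exploratory, so adherence is not ruled out, and the documents do not say how many adherent participants or non-drinkers were enrolled.

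**Conclusion.** The point holds as a failure to commit. The article fixes four randomisation strata and then leaves both factors, and baseline drinking, to an undefined judgement. The error is in the conservative direction and does not threaten validity.

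Its size depends on what finally enters the model: about 5 to 20% excess SE with none of the three (R² of 10 to 30%, assumed), about 4 to 8% with T0 only as a response (ρ of 0.5 to 0.7, assumed), and close to nil for the primary outcome with baseline drinking as a covariate. A direct gender effect with R² of 0.02 would change the SE by only about 1%. The figures come from linear models. They carry over only roughly to the negative binomial models, and in the logistic models adding covariates also changes the effect being estimated. The moderator gap is smaller and concerns interpretation, not error. Overall this is a modest point, worth settling before the data are analysed.

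**What to change.** In Statistical Analyses, replace the conditional covariate sentence with a fixed rule:

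- Gender and guideline-adherence stratum, with the values used for randomisation in Castor, enter every primary and secondary outcome model as fixed effects, with the baseline value of that outcome where one is measured.
- If T0 is kept as a response, baseline enters through the response and not a second time as a covariate. Stratum-by-time terms are then added, because a stratum main effect alone cannot absorb differences between strata in change.
- In logistic and negative binomial models, label the adjusted arm effect as conditional on these covariates.
- Add arm by guideline adherence to the exploratory moderators and report the arm effect, with its interval, in each adherence stratum.

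The cost is wording only. Both factors were needed to randomise and the baseline outcomes are collected at T0, so no new data are required. The change should be dated before the outcome data are analysed by arm.
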